### 2.8 Data management and monitoring

All data will be obtained from the medical records completed by the researcher. Data will be collected using an electronic case report form. The data manager is responsible for managing data and establishing a dedicated database for the project. Data entry will be performed by trained personnel, who will subsequently ensure data quality and accuracy. To ensure data accuracy, two data administrators will independently perform double entries and proofreading. Table 2 presents the details of the data-collection process.

**TABLE 2 T2:** Study data collection process.

Study period											
Research stage	Enrolment	Intervention			Follow-up						
Visit number	1st	2nd	3rd	4th	5th	6th	7th	8th	9th	10th	11th
**Time point**	**Day 0**	**Day 30**	**Day 60**	**Day 90**	**Month 6**	**Month 9**	**Month 12**	**Month 18**	**Month 24**	**Month 30**	**Month 36**
Baseline basic information collected											
Eligibility screen	✔										
Informed consent	✔										
Demographic information	✔										
Medical and treatment history	✔										
Combined disease	✔	✔	✔	✔	✔	✔	✔	✔	✔	✔	✔
Combined medication	✔	✔	✔	✔	✔	✔	✔	✔	✔	✔	✔
Observation indices											
Recurrence and metastasis	✔	✔	✔	✔	✔	✔	✔	✔	✔	✔	✔
CTCs	✔			✔							
Vital signs	✔	✔	✔	✔							
Adverse reactions	✔	✔	✔	✔							
TCM Symptom Scale	✔	✔	✔	✔							
FACT-C	✔	✔	✔	✔							
ESAS	✔	✔	✔	✔							
Tumour markers	✔	✔	✔	✔							
Imaging examination	✔	✔	✔	✔	✔	✔	✔	✔	✔	✔	✔
Safety observations											
Routine blood tests	✔	✔	✔	✔							
Blood biochemistry tests	✔	✔	✔	✔							
Routine urine and stool test	✔	✔	✔	✔							
ECG	✔	✔	✔	✔							
Adverse events	✔	✔	✔	✔							

CTCs, circulating tumour cells; ECG, electrocardiography; ESAS, edmonton symptom assessment scale; FACT-C, functional assessment of cancer therapy-colorectal; TCM, traditional Chinese medicine.

### 2.9 Sample size calculation

The sample size was estimated using the PASS software (version 11; NCSS, LLC, Kaysville, UT, United States) and a log-rank test. The final sample size depends on several factors, including the occurrence of primary endpoint events.

The main endpoints of this study will be the postoperative recurrence and metastasis of stage II and III CRC. In previous studies (Xu et al., 2017; Yang et al., 2008), the 3-years recurrence and metastasis rates in the treatment and control groups were 18 and 31%, respectively. In this study, we used a 1:1 distribution design and an 80% test efficiency. The false-positive error rate will be controlled within 5% (both sides), and the annual loss rate in the follow-up period will be controlled within 5%. Based on the above hypothesis, 342 patients (171 and 171 in the experimental and control groups, respectively) were enrolled after a 1-year recruitment period and 3-years follow-up period. The number of expected endpoint events is 88 (33 in the experimental group and 55 in the control group). A minimum of 342 patients is required. This study will enrol 350 patients (175 in each group).

### 2.10 Statistical analysis

Statistical analyses will be performed using the SAS statistical analysis software (version 9.4; SAS Institute Inc., Cary, NC, United States). Data will analysed at the end of the study.

#### 2.10.1 Selection of analytical data sets

1) *Full analysis set:* The ideal set of participants will match the principle of intentionality analysis (mainly including all randomised participants) as closely as possible. The dataset was obtained by eliminating all randomised participants using the smallest and most reasonable method.2) *Compliance scheme set:* In compliance with the experimental treatment scheme, the main variables can be measured, baseline variables will not be missing, and no major violations of the experimental scheme will be observed.3) *Safety set:* All participants will receive at least one treatment after randomisation.4) The full analysis set and compliance scheme set will be subjected to curative effect analysis, whereas the full analysis set will be used to analyse demographic and other baseline characteristics and therapeutic indicators.

#### 2.10.2 Contents of statistical analysis

The statistical analysis will include the actual number of participants enrolled in the two groups, dropouts, excluded cases, demographic and other baseline characteristics, compliance, efficacy, and safety analyses.

#### 2.10.3 Statistical analysis method

1) Descriptive statistical analysis: Qualitative indicators will be described using frequency tables, percentages, or constituent ratios, while quantitative indicators will be described using mean and standard deviation or median, lower quartile (Q1), upper quartile (Q3), minimum, and maximum.2) Two groups of comparative analyses will be conducted. For qualitative data, the chi-square test, Fisher’s exact probability method, Wilcoxon rank-sum test, Cochran–Mantel–Haenszel-2 test, and weighted least-squares covariance test will be used. Quantitative data will be tested for normal distribution using a *t*-test (homogeneity test of variance between groups with a test level of 0.05, and the Satterthwaite method for correction of the *t*-test results when the variance is uneven). The Wilcoxon rank-sum test will be used in cases of non-conformity to the normal distribution, Kaplan–Meier survival analyses will be performed, and the Cox proportional risk model will be used for survival data. The hypothesis test uses a bilateral test and generates test statistics and corresponding P values. The test level will be set at 0.05, and statistical significance will be set at P < 0.05.

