#### 2.6.2 Secondary outcomes

1) Quality of life score will be measured as follows:a) TCM symptom grade (Appendix 1) with the evaluation standards listed in Table 1.b) Functional Assessment of Cancer Therapy-Colorectal (FACT-C) (Version 4) scale (Appendix 2)*.* The FACT-C scale is divided into five grades: not at all (0), slightly (1), somewhat (2), quite a bit (3), and very much (4). Positive items (i.e. the higher the grade, the better the quality of life) will be directly scored from 0 to 4, whereas negative items will be reverse-scored. Items 1–7, 15, 17–20, 28, 29, 32, 35, and 36 are negative items. The scoring formula is as follows: forward item score = (0 + answer option number); reverse item score = (4 − answer option number). If there will be any unanswered questions, the score will be calculated by adding the scores of the answered questions to the total number of questions answered. The scores of all the fields will be summed to obtain the total score.c) Edmonton Symptom Assessment Scale (ESAS) (Appendix 3)*.* The scale uses a digital scoring method, with each symptom scored between 0 (asymptomatic) and 10 (most serious). Patients will choose a number to express their feelings, with a higher number indicating more serious symptoms. The points will be divided into three degrees: mild, 1–3; moderate, 4–6; and severe, 7–10.2) Circulating tumour cells (CTCs) will be counted in the peripheral blood after randomisation and 3 months later.

**TABLE 1 T1:** Treatment efficacy according to TCM Symptom Scale Score.

Effect level	Definition
Significantly effective	TCM Symptom Scale score decreased by >50% after versus before treatment
Effective	TCM Symptom Scale score decreased by 30–50% after versus before treatment
Ineffective	TCM Symptom Scale score decreased by <30% after versus before treatment

TCM, traditional Chinese medicine.

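### The tests named for FACT-C, ESAS and CTC make no baseline adjustment and the TCM score is graded in percent-change classes: valid, but less precise than the collected data allow

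*Protocol article*

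**What the plan says.** Section 2.10.3 sets out the methods by type of data.

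- **Quantitative data:** a two-group t-test, with the Satterthwaite correction when variances differ. If normality fails: "The Wilcoxon rank-sum test will be used in cases of non-conformity to the normal distribution". No covariate and no model across visits is named.
- **Qualitative data:** a list that includes chi-square, Wilcoxon, Cochran–Mantel–Haenszel and a weighted least-squares covariance test, with no stratum or covariate given.
- **Survival data:** Kaplan–Meier, and "the Cox proportional risk model will be used for survival data".
- **Level:** "The test level will be set at 0.05, and statistical significance will be set at P < 0.05".

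Section 2.6.2 makes the TCM symptom grade, FACT-C, ESAS and CTCs secondary outcomes. Table 1 turns the TCM score into three classes. The top one is "TCM Symptom Scale score decreased by >50% after versus before treatment", the middle one a fall of 30–50%, and the bottom one a fall of less than 30%.

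Table 2 in section 2.8 schedules the three scales at Days 0, 30, 60 and 90, and CTCs at Days 0 and 90.

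**The concern.** A baseline score usually predicts the follow-up score of the same patient. A two-sample test on follow-up scores leaves that predictable part in the error term. A test on change scores removes it only imperfectly, because subtracting the whole baseline adds noise when the correlation is below 1. The section names no method that uses the Day 30 and Day 60 scores together with Day 90, although the Discussion says that changes in quality of life over the treatment period will be monitored.

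Grading the TCM score in three classes discards more. Patients on either side of a cut are treated as different and patients within a class as equal, and the percentage depends heavily on a small denominator.

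What is at stake is the width of the intervals and the power for the secondary outcomes. The error rate of the tests is not in question.

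**Working it through.** **The plan's own figure.** The only calculated figures are for disease-free survival (section 2.9). The rates of 18% and 31% at 3 years give a hazard ratio of ln(0.82)/ln(0.69) = 0.535. With exponential survival, uniform accrual over 1 year, 4 years in total and 5% annual loss, 171 patients per arm give 32.4 + 55.3 = 87.7 events. The plan states 33 + 55 = 88. The figure reproduces and does not bear on this point. The article gives no sample-size figure, standard deviation or correlation for the quality-of-life scales or CTCs.

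**Inputs.** From the plan: 175 patients per arm and a two-sided level of 0.05. Assumed: a correlation ρ between baseline and follow-up score of 0.3, 0.5 or 0.7, equal variance σ² at both times, and a linear relation with the same slope in both groups.

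**Variance of one patient's contribution to the group comparison**

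- t-test on follow-up score: σ²
- t-test on change from baseline: 2σ²(1 − ρ)
- ANCOVA with baseline as covariate: σ²(1 − ρ²)

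Section 2.10.3 does not say whether follow-up scores or changes are tested, so both comparisons are needed. The ratio of ANCOVA to the follow-up test is 1 − ρ². The ratio to the change test is (1 − ρ²)/[2(1 − ρ)] = (1 + ρ)/2.

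| ρ | ANCOVA ÷ follow-up test | ANCOVA ÷ change test |
|---|---|---|
| 0.3 | 0.91 | 0.65 |
| 0.5 | 0.75 | 0.75 |
| 0.7 | 0.51 | 0.85 |

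Both ratios are below 1 for every ρ strictly between 0 and 1, so ANCOVA gains on either reading. At ρ = 0.5 the 175 patients per arm carry the information of 175/0.75 = 233 analysed by either t-test.

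**Power.** The standardised effect that the follow-up t-test detects with 80% power is (1.960 + 0.842) × √(2/175) = 0.30 SD. For that effect:

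| ρ | Follow-up t-test | Change t-test | ANCOVA |
|---|---|---|---|
| 0.3 | 80% | 65.8% | 83.6% |
| 0.5 | 80% | 80.0% | 89.9% |
| 0.7 | 80% | 95.1% | 97.5% |

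These ratios are for t-tests. For CTC counts, or where the Wilcoxon test is used, they are only a guide.

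**Table 1 by arithmetic**

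- Baseline 0: the percentage has a zero denominator and no class applies.
- 1 to 0: a fall of 100%, top class.
- 2 to 1: a fall of exactly 50%, middle class.
- 20 to 15: a fall of 5/20 = 25%, bottom class.
- 20 to 25: a rise of 25%, also bottom class, since no class exists for worsening.

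The eligibility criteria in sections 2.3.1 and 2.3.2 set no minimum symptom score, so low baselines are possible.

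**Cost of the classes.** A simulation used 175 patients per arm, 2,000 runs per setting, an assumed baseline mean of 20 and SD of 6, a mean fall of 6 points and the same 0.30 SD effect:

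| ρ | Wilcoxon on three classes | Top two classes vs bottom, chi-square | ANCOVA on score |
|---|---|---|---|
| 0.3 | 67% | 57% | 82% |
| 0.5 | 80% | 69% | 90% |
| 0.7 | 92% | 86% | 96% |

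The three classes lose about 4 to 15 points of power against ANCOVA, and two classes about 10 to 25.

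**The case against.** The strongest reply is that this is a condensed article and that covariates and repeated-measures models are commonly settled in an analysis plan, which is not shown. Section 2.10.3 is a general list that ties no test to a named outcome and excludes no adjustment. This stands in part: a fuller plan may already contain ANCOVA. But the article does name the tests for quantitative data, and the point is about that stated choice.

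The reply is also right about several stronger readings that a reader might infer:

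- *Baseline is collected and never used.* Baseline is the denominator of every TCM class, and tests on change scores fit the text. What can be said is that the named tests do not adjust for it.
- *The gain is 9–51%.* That holds only against a test on follow-up scores. Against a test on changes it is 35%, 25% and 15% at ρ = 0.3, 0.5 and 0.7.
- *Patients without a Day 90 score contribute nothing.* The article states no missing-data rule for the group comparisons, and the same tests could be run at Days 30 and 60.
- *A one-point fall puts any near-asymptomatic patient in the top class.* With whole-number scores this happens only at a baseline of 1. Appendix 1 is not shown, so the score steps and the frequency of such baselines are unknown.
- *Sizing disease-free survival on an unadjusted log-rank test is an error.* It is ordinary practice, and a Cox model can carry covariates.

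**Conclusion.** The point holds as a matter of precision for the secondary outcomes. The tests stated for quantitative data are valid under randomisation. Neither bias nor a raised type I error is shown, and chance imbalance at baseline is already covered by the error rate of the tests. They are less precise than a baseline-adjusted analysis of the same data on either reading of the text: ANCOVA variance is 0.51 to 0.91 of that of the follow-up test and 0.65 to 0.85 of that of the change test, over ρ from 0.3 to 0.7. These sizes rest on assumed correlations and equal variances. The class losses rest further on an assumed TCM score distribution.

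The Table 1 defects at a baseline of 0 and for worsening need no assumption beyond the class definitions.

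Disease-free survival, the sample size and the event count are untouched. Stratifying or adjusting that analysis by stage would add about 0.5 to 3 points of power if stage III is assumed to carry 2 to 3 times the hazard of high-risk stage II. It is an option and does not repair a fault.

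**What to change.** Before unblinding, amend section 2.10.3, or the analysis plan if it is silent, as follows.

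1. Analyse FACT-C, ESAS and the continuous TCM score by ANCOVA at Day 90 with the baseline score as covariate. Alternatively, use a mixed model for repeated measures over Days 30, 60 and 90 with baseline score, visit, group and group-by-visit. Report the Day 90 difference with its 95% confidence interval.
2. Analyse CTC count with a count model adjusted for baseline CTC. Section 2.6.2 places the first sample after randomisation, so confirm that it precedes the first dose.
3. Keep the Table 1 classes as a descriptive summary. State how a baseline of 0 is handled and show worsening separately.
4. Optionally, stratify the log-rank test and the Cox model by stage.

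The cost is revised wording and slightly more programming. No new patients, visits or measurements are needed.

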## 3 Discussion

The current treatment of stage II and III CRC involves a combination of surgery, radiotherapy, and chemotherapy (Munro et al., 2015; Snelgrove et al., 2015). Prognosis is determined according to clinical stage and risk factors (Oh et al., 2019). Patients are identified as incurable once the tumour recurs and metastasizes resulting in the death of nearly all patients (Ohlsson and Pålsson, 2003; Primrose et al., 2011). For tumours with high mortality rates, it is necessary to shift the focus from diagnosis and treatment to prevention. TCM has been widely used as a medical tool in China for cancer treatment. In previous studies, approximately 60–70% of patients with cancer in China received TCM (Sun et al., 2017; Sun et al., 2018). TCM treatment is also considered part of a healthy lifestyle to improve postoperative survival (Ching and Mok, 2022). Our research team has conducted a series of studies to prove the efficacy and safety of TCM in CRC treatment (Guo et al., 2012; Xu et al., 2017). TCM practitioners have also verified its safety and efficacy for cancer prevention and treatment in clinical practice (Liu et al., 2018; Lv et al., 2019).

To improve the clinical efficacy of TCM in the treatment of CRC and promote its use, further research into disease and syndrome combinations according to the main pathogenesis of CRC using strict multicentre clinical evaluations is necessary. In this study, patients with stage III CRC and high-risk stage II CRC after radical surgery and standard adjuvant chemotherapy will be selected as primary research participants. This large-sample, multicentre, double-blind, randomised controlled trial aims to demonstrate the efficacy of TCM in treating postoperative CRC by reducing metastasis and recurrence rates and improving patient quality of life.

CRC recurrence in patients with stages II and III CRC is currently being studied by considering its recurrence mechanism and prognostic factors. Patients with stage II and III CRC who were treated with adjuvant chemotherapy had a 25% survival benefit. In personalised medicine, it is necessary to identify CRC patients who may benefit from adjuvant chemotherapy (Cheng et al., 2018). Molecular diagnostics can guide treatment decisions for these patients (Kugimiya et al., 2019; Ntavatzikos et al., 2019). Regarding tumour recurrence–related factors, an increasing number of tumour markers can significantly predict the prognosis in stage II and III CRC cases (Lino-Silva et al., 2019). In addition, these tumour markers have a direct impact on the metastasis, recurrence status, and survival time of patients with stage II and III CRC (You et al., 2019). Moreover, researchers have developed CTC-based prognostic models to predict tumour recurrence in stage II and III CRC, which can be used to identify patients at high risk of recurrence and guide aggressive treatment to improve clinical outcomes (Rothé et al., 2019; Wang et al., 2019). In this study, we dynamically observed changes in CTCs in patients after radical surgery and chemotherapy, which is a new exploration and we hope to provide a better reference for the prognosis of patients with CRC.

In conclusion, this trial will determine the efficacy and safety of JHG in preventing metastasis and recurrence of stage III CRC and high-risk stage II CRC after radical surgery and standard adjuvant chemotherapy. Changes in the patient’s quality of life during the treatment period will be monitored. Monitoring CTCs in patients before and after treatment will provide new information regarding the tumour inhibition properties of TCM. Another objective of this study is to investigate the relationship between metastasis/recurrence and CTCs.
